#### Secondary outcomes

The secondary outcome variables will be measured in the pre-implementation, peri-implementation, and post-implementation periods. The details of the outcome variables have been listed in table 1. Changes in measure (i.e., time, therapy, event rate) will be reported descriptively. The study is not powered to detect a significant change associated with the intervention; rather, these clinical process and outcome measures will provide a signal for safety and provide important feasibility information to inform future scalable studies if the protocol and co-design approach to implementation is found to be effective.

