## INTRODUCTION

Pre-eclampsia is a multisystemic disorder characterized by varied degrees of placental malperfusion.^(1)^ It is diagnosed when there is maternal hypertension coupled with new-onset proteinuria presenting on or after 20 weeks of gestation.^(2)^ Pre-eclampsia is estimated to affect 3 - 5% of pregnancies globally^(3)^ accounts for up to 15% of maternal morbidity and mortality.^(4)^ Incidence and associated morbidity and mortality is disproportionately higher in low and lower-middle-income countries affecting up to 151 in every 10,000 deliveries.^(3)^

Preeclampsia is diagnosed by a constellation of signs and symptoms, and presents as a spectrum in severity. In its simplest presentation, it is diagnosed in the presence of maternal hypertension coupled with new-onset proteinuria presenting on or after 20 weeks of gestation.^(2)^ Severe pre-eclampsia and presentation includes; non-invasive blood pressure being ≥ 160/110mmHg measured on two occasions at least 4 hours apart, the presence of thrombocytopenia (platelets less than 100,000/mL), severe persistent right upper quadrant or epigastric pain, abnormally elevated liver enzymes, progressive renal insufficiency, pulmonary oedema, and new-onset visual or cerebral disturbance.^(2)^ At its most severe, eclampsia which is defined as the occurrence of one or more generalized tonic-clonic convulsions unrelated to other medical conditions in women with hypertensive disorder of pregnancy.^(5)^ Pre-eclampsia is estimated to affect 3 - 5% of pregnancies globally.^(3)^ In Ghana, the incidence estimates vary from 2.9%^(5)^ to 9.9%.^(6)^ The incidence and burden on poor outcomes are as a result of both population characteristics and quality of and access to maternal, antenatal and obstetric services in the country.^(4)^

Potential solutions to improve outcomes in the presence of pre-eclampsia and eclampsia increasingly focus on improving recognition and on timely, effective treatment, notably through the implementation and adoption of treatment guidelines and protocols.^(7)^ A review of pregnancy-related deaths arising from pre-eclampsia/eclampsia recommended the need for hospitals and facilities to adopt and implement standard policies and protocols in the management of pre-eclampsia and eclampsia to improve outcomes.^(8)^

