### Study site

The study will be conducted at the Obstetric Emergency Unit of the Komfo Anokye Teaching Hospital. The Directorate of Obstetrics and Gynecology of the Komfo Anokye Teaching Hospital in Ghana. Komfo Anokye Teaching Hospital is a 1,500-bed facility in the Northern half of Ghana. The Directorate of Obstetrics and Gynecology is a 250-bed department with a 35-bed Emergency Unit. The annual deliveries at the hospital average 4,500 - 5,000. There is currently no protocol for managing these emergency cases, leading to variations in clinical care.

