### Study participants

The study will include all patients who present at the obstetric emergency with the clinical assessment of pre-eclampsia with severe features or eclampsia. Severe features are defined as the presence of one of the following; platelets, 100 x 109, severe persistent right upper quadrant pain, renal insufficiency (serum creatinine > 1.1mg/dL or doubling of serum creatinine in the absence of renal disease), pulmonary oedema, visual disturbance, unexplained new-onset headache unresponsive to medication and HELLP syndrome acronym from hemolysis, elevated liver enzymes and low platelets.^(13)^

Patients who present dead on arrival to the emergency unit will be excluded. There are a few patients who will not present to the ED with pre-eclampsia/eclampsia but may develop the condition days later during a hospital admission for another pregnancy-related condition. These patients will also be excluded, given the variation in their hospital journey and the likely limited number of affected patients.

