### Study timeline

There will be a three-month period of pre-implementation data collection to establish a baseline assessment of processes of care, population characteristics, and clinical outcomes. Active implementation will occur over a 6-week period, during which the research team will meet weekly with clinical stakeholders to identify potential barriers to implementation and develop solutions, including protocol adaptations and implementation strategies. After this time, the research team will step back from weekly meetings, with only data collection by trained data collectors, so as to evaluate the study outcomes.

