This study will generate new information regarding the effect of these strategies in the emergency, obstetrics, and maternal care population, drawing on perceptions and experiences from a diverse healthcare team. carefully designed with active stakeholder participation to overcome known barriers in implementation science. Stakeholder engagement before implementing a protocol enable the identification of context-specific barriers and givefosters clinicians’ sense of ownership, which improves the chances of success.^(23)^ Some Doctors and Nurses will be identified as champions to leverage their influence in the department to enhance implementation as documented in literatutre.^(31)^ Throughout the implementation period, progress will be audited periodically through data analysis to provide feedback to clinicians, as audit and feedback positively influence clinicians’ attitudes towards the implementation.^(2)^ The strategies to enhance implementation (education, stakeholder engagements, use of champions, audit, and feedback) will be employed over six weeks of active implementation. Their eventual withdrawal may pose a challenge to sustainability, but it is expected that the potential benefits in clinical outcomes and systems improvement would drive sustainability.

The success of these implementation strategies will be evaluated using the RE-AIM framework's 3 domains (fidelity, reach, and adoption). The RE-AIM framework is an effective tool for systematically evaluating healthcare interventions.^(32)^

Despite this study's purposeful selection of strategies to support context adaptation and engagement from clinical stakeholders, there is no assurance of success. The findings of the study will determine the ease of adoption and implementation of this clinical protocol, identify barriers and facilitators of the implementation process, and assess the impact on maternal outcomes specific to both the hospital and potentially relevant to the wider Ghanaian healthcare system. Though a single-center study, the findings may still serve as a guide for future policy implementation on a broader scale.

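### The safety-signal claim for descriptive before/after changes is not limited for rare outcomes such as maternal death, where a true doubling could often show as no increase

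*Protocol article*

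**What the plan says.** In the analysis plan, under Secondary outcomes, the protocol article measures these variables before, during and after implementation. On the analysis it says: "Changes in measure (i.e., time, therapy, event rate) will be reported descriptively". It then concedes that the study lacks power for the clinical outcomes, and offers in place of power that "these clinical process and outcome measures will provide a signal for safety", together with feasibility information for later studies.

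Table 1 lists the measures in one block covering intervention effect and patient safety. Maternal hospital and ICU mortality stand there beside treatment times, fluid volume, length of stay, ICU admission and the fetal outcomes.

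The Discussion says the findings will "assess the impact on maternal outcomes specific to both the hospital", with possible relevance to the wider health system.

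On size and duration:
- Study site: "The annual deliveries at the hospital average 4,500 - 5,000".
- Introduction: incidence of pre-eclampsia in Ghana between 2.9% and 9.9%.
- Study participants: only women "with the clinical assessment of pre-eclampsia with severe features or eclampsia" are eligible.
- Study timeline: "There will be a three-month period of pre-implementation data collection" and "Active implementation will occur over a 6-week period".

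The article gives no expected number of patients, no baseline death rate and no length for the post-implementation period, although adoption is measured in the sixth month.

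**The concern.** The sentence on safety covers every outcome in Table 1, including maternal death, the most serious and probably one of the rarest. With a few dozen to about a hundred women in the baseline, the expected number of deaths is very small, and a bare difference between two such counts is dominated by chance. A protocol that doubled the risk of death could show no increase, and one that changed nothing could show an apparent doubling.

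The study is meant to inform larger studies, and the Discussion also looks to wider policy use. A table with no visible rise in deaths, read under an unqualified promise of a safety signal, could be taken as reassurance that the data do not give.

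**Working it through.** The plan states no sample size, power or alpha, so there is no figure of its own to reproduce. The check derives a rough caseload from the article and asks how a bare comparison of rates would behave.

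**1. Caseload (figures from the article)**
- Per year: 4,500 × 0.029 = 130.5 to 5,000 × 0.099 = 495.
- Three-month baseline: 130.5/4 = 33 to 495/4 = 124.
- Six weeks: 130.5 × 6/52 = 15 to 495 × 6/52 = 57.
- Post period, **assumed** to run from the end of the six weeks to month 6, which is 26 − 6 = 20 weeks or about 4.5 months: 130.5 × 20/52 = 50 to 495 × 20/52 = 190.

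The comparisons are therefore 33 v 50 (low), 124 v 190 (high) and, near the middle, 80 v 120. The range is a proxy and not a bound. It applies national incidence at all severities to one hospital's deliveries, while the cohort is severe disease seen at the emergency unit.

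**2. Chance that a true doubling shows as no increase**

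Let X ~ Bin(n₁, p) be deaths before and Y ~ Bin(n₂, 2p) deaths after. The quantity is P(Y/n₂ ≤ X/n₁), summed exactly over both binomials. Baseline mortality p is **assumed**, because the article gives none.

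| Baseline v post | p = 1% | p = 2% | p = 5% |
|---|---|---|---|
| 33 v 50 | 48% | 33% | 21% |
| 80 v 120 | 31% | 22% | 10% |
| 124 v 190 | 25% | 15% | 4% |

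Expected deaths show why. At 2%, 33 women give 33 × 0.02 = 0.7 deaths at baseline, and 50 women at 4% give 50 × 0.04 = 2.0 afterwards.

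For baseline against the six-week period at 2%, the doubling shows as no increase in 55% (33 v 15) or 23% (124 v 57).

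**3. The opposite error**

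With no true change at 2%, in the three comparisons tabled above, deaths appear to rise in 42% to 49% of studies and to at least double in 21% to 33%. The first figure is near what any comparison without a threshold gives, whatever its size. The second reflects the small numbers.

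**4. What zero deaths would exclude**

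The exact 95% upper limit for 0/n is 1 − 0.025^(1/n):
- 0/15: 21.8%
- 0/33: 10.6%
- 0/57: 6.3%
- 0/124: 2.9%

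**5. Commoner outcomes (assumed rates)**

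By the same enumeration, a rise from 10% to 20% shows as no increase in 11% (33 v 50) or under 1% (124 v 190). A rise from 30% to 45% is missed in 8% or under 1%.

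**The case against.** The strongest reply is that the article already says it is underpowered for these outcomes and speaks only of a signal that informs later work. Success is defined by fidelity, reach and adoption. Nowhere does the article say that an absence of observed deaths means the protocol is safe. The decisive inputs, baseline mortality and post-period length, are assumptions, and at 5% mortality with the high caseload a doubling is missed in only 4% of studies.

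Much of this stands, and it limits the point. A reader might infer that the safety claim fails altogether. The documents do not support that: the sentence covers many outcomes, and the commoner ones can show a signal at these numbers. A reader might also infer that the comparison of deaths is no better than chance in both directions. At an assumed 2%, however, a real doubling does appear as an increase in 67% to 85% of studies. Nor is it fair to say that the safety measures were not fixed in advance. Table 1 lists them under a patient-safety label, and further labelling of endpoints or harmful directions is detail that a condensed article may leave out.

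What the reply does not remove is the unqualified wording. Conceding low power and then promising a safety signal instead leaves maternal death inside the promise. Intervals could be left to a fuller document, but the article itself fixes both the descriptive reading and the claim drawn from it.

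**Conclusion.** The point holds for rare outcomes only. As worded, the plan promises a safety signal from bare before/after changes without excepting events such as maternal death. At the caseload its figures suggest, and with a post period of about 4.5 months, a true doubling of deaths would show as no increase in 25% to 48% of studies at 1% mortality, 15% to 33% at 2% and 4% to 21% at 5%. Whether misses are frequent therefore depends on mortality and caseload that the documents do not fix. Fewer eligible women, because only severe disease counts, would make it worse; referrals would make it better.

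This is a defect in what is claimed from the secondary outcomes. It does not touch the primary implementation outcome, and it is no reason to drop the descriptive approach. It should be corrected because the remedy is nearly free.

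**What to change.** In the analysis plan, under Secondary outcomes, keep the reporting descriptive and make three changes:

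- For the event outcomes, give n/N with an exact 95% interval in each period, and a 95% interval for the post-minus-pre difference.
- Replace the general promise of a safety signal with a statement limited to the largest increase those intervals exclude.
- Add that no observed increase in rare events such as maternal death is not evidence of safety.

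In the Discussion, bring the sentence on assessing impact on maternal outcomes into line with this, for example by saying that the study will describe those outcomes and the uncertainty around them.

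The cost is a few table columns, a short rewording in two places and a less favourable stated claim. No additional patients or data are needed.

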## DISCUSSION

Pre-eclampsia and eclampsia are among the top five causes of maternal mortality in Sub-Saharan Africa.^(37)^ In Ghana, it is one of the top two causes of maternal mortality.^(38)^ Given its significant contribution to maternal mortality, any intervention that improves maternal outcomes in that cohort of patients will considerably impact overall maternal outcomes.

Standardized policies and protocols for clinical care have been shown to improve outcomes,^(39)^ but the generally poor uptake requires the use of systematic processes to overcome implementation barriers and identify potential facilitators.

Studies have identified barriers to the adoption of evidence-based practices in maternal and obstetric care. These include: staffing gaps, lack of clinical knowledge, lack of resources, lack of organizational support, and behaviors and beliefs that may lead to guidelines being perceived as competing with other clinical priorities or in conflict with clinician autonomy.^(1,2)^ Furthermore, a lack of buy-in from medical staff and inadequate stakeholder needs assessment may also limit implementation and adoption.^(40)^

This study is designed to assess the effectiveness of implementation strategies and stakeholder co-design in improving the management of pre-eclampsia and eclampsia. Improving management and outcomes for this population requires healthcare teams from different specialties to work collaboratively, often rapidly (i.e., within the first hour of admission), and to support ongoing management, often during the transfer of patients between emergency units, operating theatres, and, sometimes, intensive care.^(41)^ The complexity of this patient care pathway means it is critical to identify, and hopefully mitigate potential barriers to policy adoption and practice change, prior to wider scaled implementation. Furthermore, this patient population is vulnerable, and both mother and baby are exposed to significant risk of morbidity and mortality if the condition is not optimally managed.^(42)^

This study will generate new information regarding the effect of these strategies in the emergency, obstetrics, and maternal care population, drawing on perceptions and experiences from a diverse healthcare team. carefully designed with active stakeholder participation to overcome known barriers in implementation science. Stakeholder engagement before implementing a protocol enable the identification of context-specific barriers and givefosters clinicians’ sense of ownership, which improves the chances of success.^(23)^ Some Doctors and Nurses will be identified as champions to leverage their influence in the department to enhance implementation as documented in literatutre.^(31)^ Throughout the implementation period, progress will be audited periodically through data analysis to provide feedback to clinicians, as audit and feedback positively influence clinicians’ attitudes towards the implementation.^(2)^ The strategies to enhance implementation (education, stakeholder engagements, use of champions, audit, and feedback) will be employed over six weeks of active implementation. Their eventual withdrawal may pose a challenge to sustainability, but it is expected that the potential benefits in clinical outcomes and systems improvement would drive sustainability.

The success of these implementation strategies will be evaluated using the RE-AIM framework's 3 domains (fidelity, reach, and adoption). The RE-AIM framework is an effective tool for systematically evaluating healthcare interventions.^(32)^

Despite this study's purposeful selection of strategies to support context adaptation and engagement from clinical stakeholders, there is no assurance of success. The findings of the study will determine the ease of adoption and implementation of this clinical protocol, identify barriers and facilitators of the implementation process, and assess the impact on maternal outcomes specific to both the hospital and potentially relevant to the wider Ghanaian healthcare system. Though a single-center study, the findings may still serve as a guide for future policy implementation on a broader scale.

## Data Availability

The contents underlying the research text are included in the manuscript.
